**Fig. 1 Fig1:**
[figure not shown]
Schematic diagram. FD, functional dyspepsia; fMRI, functional magnetic resonance imaging

**Table 1 Tab1:** Schedule of enrollment, interventions, fMRI scan, and assessment

Study period week	Baseline		Treatment period				Follow-up			
Time point	^**a**^***0-wk.***	***1-wk.***	***2-wk.***	***3-wk.***	***4-wk.***	***5-wk.***	***6-wk.***	***7-wk.***	***8-wk.***	***9-wk.***
**Enrolment**										
Patient screen										
Informed consent	★									
Physical examination		★								
Laboratory test		★								
Randomization		★								
**Interventions**										
Acupuncture group			★	★	★	★				
Moxibustion group			★	★	★	★				
**fMRI scan**										
Acupuncture group		★				★				
Moxibustion group		★				★				
**Assessment**										
SF-LDQ		★				★				★
NDI		★		★		★				★
SID		★		★		★				★
SAS and SDS		★		★		★				★
HRV		★				★				
*Deqi* Sensation			★			★				
Safety monitoring	★	★	★	★	★	★	★	★	★	★

^a^The screening visits

*wk.* week, *SF-LDQ* short form Leeds Dyspepsia Questionnaire, *NDI* Nepean Dyspepsia Index, *SID* Severity Index of Dyspepsia, *SAS* Zung Self-Rating Anxiety Scale, *SDS* Zung Self-Rating Depression Scale; *HRV* heart rate variability

The study will adhere to the declaration of Helsinki principles (World Medical Association version, 2013) [23]. All participants will be asked to sign the informed consent form before enrollment in this trial. The protocol has already been ethically reviewed and approved by the Sichuan Regional Ethics Review Committee on Traditional Chinese Medicine (ID:2021KL-059) in July 2021 (Supplementary file 1) and registered on the Chinese Clinical Trial Registry (https://www.chictr.org.cn/) (ID: ChiCTR2100049496). The study will follow the Standard Protocol Items: Recommendations for Interventional Trials (SPIRIT) guidance for protocol reporting (Supplementary file 2) [24].

### Participants

#### Recruitment

The FD patients will be recruited from the outpatient department of the Hospital of Chengdu University of Traditional Chinese Medicine (TCM) and the campus of the Chengdu University of TCM from September 2021 to December 2022. WeChat, posters, leaflets, free medical consultations, etc., will be used to inform and recruit potential FD patients. All potential FD patients will undergo a physical examination and laboratory tests, including normal gastroduodenoscopy, upper abdominal ultrasound, routine blood, urine and stool test, and blood biochemical test (ALT, AST, BUN, and Scr, etc.). A qualified digestion physician will make the final diagnosis for each potential FD patient.

#### Inclusion criteria

Patients will be enrolled if they meet all the following criteria: (1) right-handed and aged 18 to 40 years, (2) matching the Rome IV diagnosis criteria for FD (Supplementary file 3), (3) having no gastroduodenal structural diseases after gastroduodenoscopy screening, (4) having not taken any gastrointestinal prokinetic drugs at least 15 days before enrollment, (5) having not involved in other clinical trials, (6) having not any contraindications to MRI scan, and (7) signing an informed-consent form voluntarily (participants or their immediate family members).

#### Exclusion criteria

The patient will be excluded if they meet any of the following criteria: (1) being unconscious or being unable to cooperate in assessment; (2) suffering from cardiovascular, neurological, renal, liver, or blood diseases; (3) women being pregnant or lactating; (4) suffering from mental disorders such as anxiety or depressive disorder, bipolar disorder, schizophrenia, and claustrophobic syndrome; (5) having a history of head trauma, migraine, or dysmenorrhea; and (6) having received acupuncture or moxibustion treatment in the past month.

### Allocation and randomization

Eligible patients will be randomly allocated in a 1:1 ratio to the acupuncture or moxibustion group. An independent researcher will generate the random sequence by PASS 15.0 (NCSS, LLC. Kaysville, Utah, USA). Every random sequence number will be sealed in an opaque envelope by another research coordinator. The acupuncturists will finally open the sealed envelope to learn the group allocation of a participant prior to the delivery of the initial intervention session.

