### Blinding

It is difficult to blind acupuncturists and patients in this trial for different types of intervention. Acupuncturists will not participate in any outcome assessment process. All the outcome assessors and statisticians will be masked in randomization assignments and intervention during the whole study.

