### Sample size calculation

The sample size was estimated based on the results of a study on the changes in the short form Leeds Dyspepsia Questionnaire (SF-LDQ) in response to a 4-week acupuncture intervention versus moxibustion intervention, which showed a mean improvement of the SF-LDQ was − 5.62 ± 2.81 (mean ± SD) in the acupuncture group and − 3.56 ± 2.62 in the moxibustion group respectively [25]. It provides an effect size (Cohen's *d* = 0.758) to estimate the sample size of this study. To achieve 90% statistical power (*α* = 0.05), at least 76 participants are needed. Besides, assuming a 20% attrition rate, ninety-two participants (46 participants per group) will be recruited to detect a two-sided significant difference. The sample size calculation steps are shown in Supplementary file 4.

According to previous fMRI-based studies [26, 27], thirty subjects or more can notably improve the reliability of results. Considering the dropout rate or loss of data due to head motion during fMRI scanning, in this study, thirty-six participants in each group will be randomized to fMRI scans.

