### Interventions

Participants in both groups will receive 20 sessions of acupuncture or moxibustion treatment in 4 weeks. Five times per week on *Zhongwan* (CV-12) and *Zusanli* (ST-36) will be selected as the treatment acupoints, which are the most commonly used acupoints for FD [28]. The locations of the acupoints are shown in Fig. 2A and Supplementary Table 1. All treatments will be performed by two acupuncturists. With at least 3 years of clinical experience and certified a 2-day standard training course.

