### Data management

Clinical data will be managed with printed case report forms and electronic data capture (EDC). An independent data administrator will keep the data. Only principal investigators have the access to the full dataset and will perform double-data entry. The evidence-based medicine center of the CDUTCM is responsible for monitoring the study and data every 3 months and will make the final decision to terminate the trial. We will publish our results in peer-reviewed journals.

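### The unblinded acupuncturists who treat every patient open the allocation envelopes themselves: an avoidable weakness in concealment, not a demonstrated bias

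*Protocol article*

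**What the plan says.** The protocol article, under Allocation and randomization, describes three steps.

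- Generation: "An independent researcher will generate the random sequence by PASS 15.0".
- Sealing: "Every random sequence number will be sealed in an opaque envelope by another research coordinator".
- Opening: "The acupuncturists will finally open the sealed envelope to learn the group allocation of a participant prior to the delivery of the initial intervention session".

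The ratio is 1:1 ("Eligible patients will be randomly allocated in a 1:1 ratio to the acupuncture or moxibustion group"). Under Interventions, "All treatments will be performed by two acupuncturists", which covers both groups. Under Blinding, "It is difficult to blind acupuncturists and patients in this trial for different types of intervention". The same section keeps acupuncturists out of outcome assessment and masks assessors and statisticians.

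Table 1 places informed consent at 0-wk, randomization and the baseline SF-LDQ at 1-wk, and the interventions from 2-wk. Under Recruitment, a digestion physician makes the final diagnosis.

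**The concern.** Concealment works when nobody with an interest in a patient's arm can learn or alter it before the patient is irrevocably committed to it. The first two steps respect this. The third gives the sealed paper to the people who will deliver the treatment, who cannot be blinded and who may think one therapy suits some patients better. Because randomization sits in an earlier week of Table 1 than the first session, there is also an interval between the allocation and its stated opening. In that interval an envelope could be opened early, or the envelopes used out of order.

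The primary outcome is the improvement in a symptom questionnaire, in patients who know their treatment. If allocation were steered, the arms would differ in prognosis from the start. Masked assessors and an intention-to-treat analysis would not correct that, because both take the allocation as given.

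**Working it through.** **Reading the sections together.** The article states no figure for this point, so the check is first one of roles and timing.

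| Step | Who | When |
|---|---|---|
| Consent | Participant | 0-wk |
| Final diagnosis | Digestion physician | At recruitment; week not given |
| Sequence generation | Independent researcher | Not stated |
| Sealing | Another coordinator | Not stated |
| Randomization, baseline SF-LDQ | Not stated | 1-wk |
| Opening the envelope | Acupuncturist | Before the first session |
| Treatment, both arms | The same two acupuncturists | From 2-wk |

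Two things follow. The person who opens is also the person who treats. And the article does not give acupuncturists any part in screening, enrolment, or the making or ordering of the sequence.

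**Illustration of size.** Inputs from Sample size calculation: SDs of change 2.81 and 2.62; mean improvements 5.62 and 3.56; 46 per arm.

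- Planned difference: 5.62 − 3.56 = 2.06.
- Pooled SD: √((2.81² + 2.62²)/2) = 2.717. This gives d = 2.06/2.717 = 0.758, the article's own effect size.
- Standard error of the difference at 46 per arm: 2.717 × √(2/46) = 0.566.

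Assumptions, none of them from the article:

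- A share f of patients has its arm decided by prognosis and not by the list.
- Steered patients in one arm have an expected SF-LDQ change 1 point better than average, and those in the other arm 1 point worse.
- The treatments do not differ.
- All 92 patients are analysed.

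Each arm mean then moves by f × 1 point in opposite directions, so bias = 2f. The type I error is the two-sided rejection probability of the t-test at the 5% level with 90 degrees of freedom and noncentrality 2f/0.566.

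| Share steered | Bias (points) | Share of 2.06 | Noncentrality | Type I error |
|---|---|---|---|---|
| 10% | 0.2 | 10% | 0.35 | 6.4% |
| 20% | 0.4 | 19% | 0.71 | 10.8% |
| 25% | 0.5 | 24% | 0.88 | 14.1% |

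The table shows what steering would cost if it happened. It does not show that it will.

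**The case against.** The case for leaving the procedure alone is substantial. Two people other than the therapists make and seal the sequence, in opaque envelopes. Consent precedes randomization, and a physician decides the diagnosis. The baseline SF-LDQ is already scheduled before treatment. The timing in Table 1 can be read as reassuring: if a number is tied to a named patient at randomization in week 1, opening the envelope later only reveals an arm that is already fixed, and changing who starts first alters nobody's arm. A therapist must in any case learn the arm before delivering it. Finally, envelope numbering, custody and logging are details that a journal article commonly leaves to the full protocol, so their absence here is no fault.

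Most of this stands, and it lowers the risk. It does not remove it, because the point rests on a step the article does state: who opens the envelope. The article does not say that the number is bound to a patient before that moment.

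Two stronger readings are tempting, and neither is supported.

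- A reader might infer that the acupuncturists control the next assignment. The article gives them no role in enrolment, eligibility, custody of the envelopes or their order.
- A reader might infer that, having seen every past assignment, they can predict the next one and so inflate the type I error. That requires a restricted list, which the article does not describe (it states only the 1:1 ratio), and influence over who enters next. Nor does that knowledge come from opening envelopes: two people who treat everyone know the past assignments whoever opens them.

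**Conclusion.** The point holds as an avoidable weakness. The last step of concealment lies with two unblinded people who deliver both treatments, and it is set some time after randomization. The article gives no sign of actual subversion, so no claim can be made that the comparison is biased or that the 5% error rate fails. The illustrative bias of 0.2 to 0.5 point and type I error of about 6% to 14% depend wholly on the assumed 10% to 25% steered and the assumed 1 point either way. With no steering, both effects vanish. It is worth changing because the remedy costs little, not because harm has been shown.

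**What to change.** Replace the last sentence of Allocation and randomization so that acupuncturists neither hold nor open envelopes. The existing coordinator or the independent researcher, provided that person does not treat patients, should:

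1. tie each sequence number to a named participant, in order of enrolment;
2. confirm that the baseline SF-LDQ is recorded;
3. only then release that participant's arm to the acupuncturist, with a time-stamped entry in a log or in the electronic data capture system that the article already names ("Clinical data will be managed with printed case report forms and electronic data capture (EDC").

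The baseline questionnaire stays where Table 1 puts it. No extra patients or visits are needed. The cost is a revised sentence, a log or a release form in the data system, and the need for that person to be reachable before each of up to 92 first sessions. The change does not stop the acupuncturists from knowing past assignments, since they treat everyone. It takes from them the chance to open an envelope early or out of order.

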### Blinding

It is difficult to blind acupuncturists and patients in this trial for different types of intervention. Acupuncturists will not participate in any outcome assessment process. All the outcome assessors and statisticians will be masked in randomization assignments and intervention during the whole study.

### Withdrawal criteria and management

Participants will be withdrawn from the trial if (1) participants develop the serious disease, (2) seriously adverse events happen, and (3) participants request to withdraw from the trial, voluntarily. The reasons and exit time will be recorded in standard case report forms (CRFs). Patients who withdraw from the trial for any reason will be considered a drop-out. All the information from participants who have dropped out will be used for intention-to-treat (ITT) analysis.

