## Methods/design

### Design and setting

The present study is a single-center, parallel-controlled, equivalence, randomized clinical trial, and a total of ninety-two patients with FD will be recruited. These patients will be randomly allocated into either the acupuncture group or the moxibustion group with a 1:1 ratio. The study period includes a 1-week baseline, 4 weeks of treatment, and another 4 weeks of follow-up. Clinical measurements will be performed at the baseline, at the end of the treatment, and at the end of follow-up, respectively. Neuroimaging scans will be performed at the baseline and the end of the treatment. More details of the study design are shown in Fig. 1 and Table 1.

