#### Primary outcome measurements

Our primary outcome is the improvement of SF-LDQ after 4 weeks of treatment. The SF-LDQ is a validated and reliable tool to measure the frequency and severity of five dyspeptic symptoms (epigastric pain, postprandial fullness, indigestion, epigastric burning, and postprandial nausea) [32]. Graded on a 5-point Likert scale, the higher the score of the five symptoms, the more severe the disorder.

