### Data analysis

#### Clinical data analysis

All analyses will be done on the ITT population. An independent statistician will conduct clinical data analysis with SPSS 24.0 software (SPSS Inc., Chicago, IL, USA). Kolmogorov–Smirnov test will be used to analyze data distribution, and Levene’s test will be used to analyze homogeneity of variance. The quantitative variables will be presented as mean and SD or median and interquartile, whereas qualitative measures will be reported as percentages with 95% CI. Analysis of variance (ANOVA) test will be used with Bonferroni post hoc comparisons for continuous variables. The independent-samples *t*-test or the Mann-Whitney *U* test for continuous variables and the chi-square test, Fisher exact test, or Kruskal–Wallis test for categorical variables will be used, when suitable. We will describe 24-h HRV using time-domain measurements. Time-domain indices of HRV quantify the amount of variability in measurements of the interbeat interval (IBI), which is the time period between successive heartbeats. These values may be expressed in original units or as the natural logarithm (Ln) of original units to achieve a more normal distribution [41]. Pearson's coefficient will be used for bivariate correlations. All the statistical significance threshold tests will be set to *p*<0.05 with a two-tailed test.

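### A patient withdrawn during treatment has only a baseline SF-LDQ, because withdrawal is from the trial and the primary scale is next taken at 5-wk, so the promised ITT comparison has no primary outcome to use for that patient

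*Protocol article*

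**What the plan says.** Two sections commit the trial to intention-to-treat. Withdrawal criteria and management says "All the information from participants who have dropped out will be used for intention-to-treat (ITT) analysis", and Clinical data analysis says "All analyses will be done on the ITT population".

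The withdrawal rule is worded as leaving the study altogether: "Participants will be withdrawn from the trial if (1) participants develop the serious disease, (2) seriously adverse events happen", with the patient's own request as the third ground. It continues: "Patients who withdraw from the trial for any reason will be considered a drop-out". The reason and time of exit are recorded. No assessment after exit is mentioned.

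The primary endpoint is fixed at one time point: "Our primary outcome is the improvement of SF-LDQ after 4 weeks of treatment". In Table 1 this is the 5-wk column. Table 1 marks SF-LDQ at 1-wk (baseline), 5-wk and 9-wk. It marks NDI, SID, SAS and SDS at those times and also at 3-wk. Design and setting does not mention the 3-wk assessment: "Clinical measurements will be performed at the baseline, at the end of the treatment, and at the end of follow-up, respectively".

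For comparing groups, Clinical data analysis lists, besides ANOVA, "The independent-samples *t*-test or the Mann-Whitney *U* test for continuous variables". It names no method for missing values.

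**The concern.** An ITT analysis needs outcome data on the patients randomised, or a defensible way of standing in for them. Here the withdrawal rule and the visit schedule together mean that nothing is planned that would give a post-baseline primary score for someone who leaves in the treatment weeks. For those patients the promise to use all drop-out information has no content on the primary outcome.

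This matters because the Blinding section accepts that patients will know which treatment they receive, and own request is one ground for leaving. Loss could therefore depend on arm and on how the patient is doing. The documents do not show that it will, but the design does little to guard against it. What is at stake is mainly bias in the SF-LDQ difference. The loss of power is small. A later analysis plan can choose how to handle missing values, but it cannot recover a score that was never collected.

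**Working it through.** **1. The plan's own figures.** From Sample size calculation: mean changes −5.62 (SD 2.81) with acupuncture and −3.56 (SD 2.62) with moxibustion; two-sided α 0.05; power 90%; 76 needed; 20% attrition; 92 recruited.

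- Difference = 5.62 − 3.56 = 2.06.
- d = 2.06 / √((2.81² + 2.62²)/2) = 2.06 / 2.717 = 0.758, as stated.
- A noncentral-t calculation gives 38 per arm (power 0.903), so 76 in total, as stated.
- 76 × 1.20 = 91.2, rounded up to 92, as stated.

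**2. What an early leaver contributes, by Table 1.**

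| Patient leaves | SF-LDQ available | Other scales available |
|---|---|---|
| before the 3-wk assessment | 1-wk only | NDI, SID, SAS, SDS at 1-wk |
| after 3-wk, before 5-wk | 1-wk only | the same four at 1- and 3-wk |
| after 5-wk | 1- and 5-wk; primary outcome complete | the same four at 1-, 3- and 5-wk |

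This assumes that assessment stops at withdrawal. In the first two rows there is no SF-LDQ change score. Any group comparison of improvement then omits the patient or uses an imputed 5-wk value.

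**3. How many patients.** 0.20 × 92 = 18.4, so about 18. The attrition rate has no time point and the study runs to 9-wk. Losses after 5-wk do not remove the primary outcome, so 18 is an upper planning figure.

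**4. Power.** If all 18.4 were lost by 5-wk, 73.6 patients would remain, 36 to 37 per arm. Power at d = 0.758 would be 0.887 to 0.896, against 0.949 with all 92. The cost in power is modest.

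**5. Bias, by illustration.** The documents give no outcomes for drop-outs. Assume that completers improve as planned and drop-outs do not improve. With loss fractions a (acupuncture) and m (moxibustion), the difference in all randomised is 5.62(1 − a) − 3.56(1 − m). The completer difference is 2.06 throughout.

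| Loss, acupuncture / moxibustion | All randomised | Completer figure relative to it |
|---|---|---|
| 20% / 20% | 4.496 − 2.848 = 1.65 | 2.06/1.648 = 1.25, 25% too large |
| 25% / 15% | 4.215 − 3.026 = 1.19 | 2.06/1.189 = 1.73, 73% too large |
| 15% / 25% | 4.777 − 2.670 = 2.11 | 2.06/2.107 = 0.98, 2% too small |

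Wider splits stretch the range: 0.73 with 30% / 10% loss and 2.57 with 10% / 30%.

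The result depends on the assumption. If drop-outs in both arms fell short of completers by the same amount g, the completer difference would be off by g(a − m), which is zero when loss is equal.

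**The case against.** The strongest reply is that the article does not say what happens to missing values, and that this is commonly left to an analysis plan not shown here. That stands. A reader might infer that the listed tests will delete everyone without a 5-wk score, so that the result is a completer analysis carrying an ITT label. The documents do not support that: a t-test, ANOVA or Mann-Whitney test can be run on imputed values, and the article states the intention to use drop-outs' information.

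Three other stronger readings also fail.

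- **That 20% will be missing at 5-wk.** The rate is a planning figure with no time point, and some of it may fall in follow-up.
- **That the sample size contradicts ITT.** Raising recruitment to allow for attrition protects power and does not define who is analysed.
- **That early leavers leave no partial information.** NDI and SID at 3-wk both measure dyspeptic symptoms and could inform imputation for anyone still present then.

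It is also fair to say that the article nowhere states that assessments end at withdrawal. That is an inference from withdrawing patients from the trial, calling them drop-outs, and listing only reason and time of exit. The inference is reasonable, and if it is wrong one sentence would settle it. Finally, the bias figures rest on assumed outcomes and assumed splits, and one split moves the result by only 2%.

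None of this touches the central point. Withdrawal rules and assessment schedules are protocol content, and both are stated here. As written, they leave the primary scale unmeasured after baseline in patients who leave during treatment.

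**Conclusion.** The concern holds in a limited form. The ITT commitment and the withdrawal rule do not fit together for the primary outcome, and the SF-LDQ schedule makes this worse by skipping the 3-wk occasion at which four other scales are taken. Up to about 18 of 92 patients could have only a baseline SF-LDQ, if all planned attrition fell before 5-wk and assessment stopped at exit.

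Under the further assumption that drop-outs do not improve, the completer difference of 2.06 would correspond to between 1.19 and 2.11 in all randomised patients across the three main loss patterns shown. The error can go in either direction. These figures show sensitivity and are not a forecast.

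It does not follow that the planned analysis is a completer analysis or that the sample size is at odds with ITT. The point is a cheap improvement to data collection, worth making because patients are not blinded and the analysis stage cannot replace scores never taken.

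**What to change.** 1. **Withdrawal criteria and management.** Distinguish stopping treatment from leaving data collection. State that SF-LDQ is still sought at 5-wk and 9-wk from anyone who stops treatment, unless that patient refuses further data collection. The grounds on which treatment stops stay as they are.
2. **Table 1 and Design and setting.** Add SF-LDQ to the existing 3-wk questionnaire set, and amend the sentence on measurement times in Design and setting so that it includes the 3-wk assessment and agrees with Table 1.

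The choice of primary model and of sensitivity analysis for missing data can be left to the SAP. A mixed model alone would not solve the problem, because a patient with only a baseline SF-LDQ adds almost nothing to the 5-wk contrast, and such a model relies on data being missing at random. Collecting the scores is the main remedy.

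The cost is one short questionnaire in a week when patients already attend five times, some follow-up contacts with patients who have stopped treatment, and a few sentences of text. The downside is slightly more data collection.
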